#### 11.4.2 Primary Analysis

Analysis of the primary objective will follow the intention-to-treat (ITT) principle. It will be based on the full analysis set (FAS). FAS will include all patients who gave informed consent. Patient data will be analysed according to their treatment allocation.

We will test if there is a difference of the LCQ score between the intervention and control group 14 days after randomization. A treatment effect of 1.3 points increase will be considered as MCID.

The hypothesis will be tested using analysis of covariance (ANCOVA). We will report the treatment effect with 95% confidence intervals (CI). Covariates of the ANCOVA model will be baseline LCQ scores, duration of cough, age, sex, and smoking status. Patients are considered as smokers, when they answer that they had smoked “more than 100 cigarettes in their life”, they smoke “daily” or “sometimes” to the participant survey (29).

Baseline characteristics of patients in the FAS will be presented stratified by group and summarized in a table.

To assess the robustness of our primary analysis, the following sensitivity analyses will be performed:

- Analysis of the primary outcome without imputing data (complete case analysis)
- Analysis of the primary outcome using the per-protocol data set (PPS) which is defined above
- Exploring interactions between covariates of the ANCOVA model of the primary analysis
- Exploring how the effect of the intervention varies among GP practices. For this, a linear mixed-model with treatment group as a fixed-effect and GP practices as a random effect will be fit.

We will conduct one subgroup analysis, comparing effects on the primary outcome in current smokers vs. current non-smokers. Subgroup effects will be analyzed by interaction tests and interpreted fully exploratory. We expect that effects are more pronounced in non-smokers according to reports by Ponsioen et al. (20).

Statistical analysis will be performed by the CTU of the University Hospital Basel using R language and environment ([www.r-project.org](http://www.r-project.org)).

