## 8.8 Study Drug Accountability

The University Hospital Basel Pharmacy is responsible for all manufacturing and logistic documentation of the study medication up to the point of distribution to the GPs. Study medication packages will be stored in appropriate conditions at room temperature in a separate room dedicated to investigational medicinal products before being handed over to the study team which is responsible for delivering it to collaborating GPs. All participating GPs will receive a package with the required and pre-randomized medication necessary to recruit up to 10 participants. GPs will be in charge for the adequate storage of the study medication package and dispensing it according to protocol.

The Hospital Pharmacy documents in its accountability log the amount, the date and medication numbers of every manufactured medication batch and the picking up by study staff.

The GP documents the acknowledgement of receipt, the inventory at the site, the dispensing of the medication to the patient, and the return or alternative disposition of unused medication. The documentation should include dates, quantities, batch number, expiry date, and medication number, and this documentation should be available to the study monitor for review upon request.

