### 11.2 Determination of Sample Size

Sample size was estimated to have 80% power to detect the minimal clinically important difference (MCID) set at 1.3 points (14).

To be able to detect an MCID of 1.3 points with a power of 80%, a total of N=204 patients need to be recruited for both arms. This was calculated without considering intra-patient correlation (IPC) correlation  $\rho$  ( $\rho$ ) between baseline and follow-up and without potential intra-cluster correlation (ICC) of patients treated by the same physician. To further increase power, we ignored  $\rho$  by calculating the sample size for a two-sample t-test with a two-sided alpha threshold of 5%. Sample size estimation was based on the assumption that individual LCQ scores are normally distributed. Chung et al. reported a standard deviation (SD) of 3.3 points (24). A recent trial with a design and study population similar to ours (15) reported a SD of 2.9.

We decided to use the more conservative assumption of 3.3 points. Due to the fact that the number of recruited patients per GP is limited to 10, ICC might remain small.

We expect a drop-out rate of 10%, similar to that in the abovementioned recent trial (15).

A less conservative choice of an SD of 2.9 and a  $\rho$  of 0.4, with the other parameters remaining the same, would have required a sample size of N=120. Hence, we assume that by the conservative choice of SD and by neglecting  $\rho$ , our calculation will sufficiently compensate for loss of power due to ICC and drop-outs. To compute the t-test, the current version of the R language and environment ([www.r-project.org](http://www.r-project.org)) function “power.t.test” of the stats package was applied.

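### The mixed model in 11.4.2 meant to show how the treatment effect varies among GP practices has no treatment-by-practice term, so as written it cannot show any variation

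*Protocol*

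**What the plan says.** Protocol 11.4.2 (Primary Analysis) specifies an ANCOVA of day-14 LCQ: "Covariates of the ANCOVA model will be baseline LCQ scores, duration of cough, age, sex, and smoking status". It then introduces a list of further analyses: "To assess the robustness of our primary analysis, the following sensitivity analyses will be performed". The last item in that list gives its aim as "Exploring how the effect of the intervention varies among GP practices". The sentence that follows ties a model to that aim: "a linear mixed-model with treatment group as a fixed-effect and GP practices as a random effect will be fit".

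Two other statements in the same section concern interactions. One list item reads "Exploring interactions between covariates of the ANCOVA model of the primary analysis". For the smoking subgroup, the protocol says "Subgroup effects will be analyzed by interaction tests and interpreted fully exploratory".

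**The concern.** The item asks whether the treatment effect differs from practice to practice. To answer that, a model needs a term through which the effect can differ: a random treatment slope by practice, or a treatment-by-practice interaction. The model named has treatment as a fixed effect and practice as a random effect. Read plainly, that is a random intercept, which describes differences between practices in the level of the outcome and not in the effect of treatment.

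If the text is followed, the report could offer this model as evidence on whether the effect is consistent across practices, although the model assumes that consistency. A reader could take a practice variance near zero, or an unchanged treatment estimate, as a sign that the effect is homogeneous. Neither would be evidence of that.

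**Working it through.** **Inputs.** MCID 1.3 points, SD 3.3, two-sided alpha 5%, power 80% and N=204 (11.2); 1:1 allocation, 102 per arm (Synopsis); 46 practices (section 1). Mean patients per practice: 204/46 = 4.43.

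**The protocol's own figure.** Per arm, n = 2(z₀.₉₇₅ + z₀.₈₀)² × SD²/Δ² = 2 × (1.960 + 0.842)² × 3.3²/1.3² = 2 × 7.85 × 6.44 = 101.2, rounded up to 102, so 204 in total. The t-based calculation gives 102.12 per arm, which is 204 when rounded to the nearest whole patient per arm. The figure reproduces, and nothing below changes it.

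**Step 1: the model as written.** For patient i in practice j, with T = 1 for prednisone and 0 for placebo:

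y_ij = b0 + b1·T_ij + u_j + e_ij

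The effect in practice j is (b0 + b1 + u_j) − (b0 + u_j) = b1. The practice term cancels, so the effect is the same in every practice and its variance across practices is 0, whatever the data.

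**Step 2: the model that matches the aim.**

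y_ij = b0 + b1·T_ij + covariates + u0_j + u1_j·T_ij + e_ij

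The effect in practice j is now b1 + u1_j, and its variance across practices is Var(u1). This is the quantity the item asks for.

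**Step 3: does another item supply the term?** No. The interactions item is limited to the ANCOVA covariates, and practice is not one of them. The interaction tests in the section belong to the smoking subgroup.

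**Step 4: simulation.** Assumptions: 204 patients spread evenly over 46 practices, simple 1:1 allocation, mean effect 1.3, total SD 3.3 before any slope variation, ICC 0.05, no covariates, and 60 simulated trials per row. The slope was tested by likelihood ratio against 5.14, the 5% point of the equal mixture of chi-square distributions with 1 and 2 degrees of freedom.

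| True SD of effect between practices | SD of effect, model as written | Median slope SD with random slope (10th to 90th percentile) | Slope test rejects |
|---|---|---|---|
| 0 | 0 | 1.2 (0.3 to 1.9) | 1 of 60 (2%) |
| 1.3 | 0 | 1.6 (0.5 to 2.4) | 10 of 60 (17%) |
| 2.6 | 0 | 2.8 (1.7 to 3.5) | 56 of 60 (93%) |

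The zeros in the second column hold to rounding error (about 10⁻¹⁵).

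**Step 5: why the corrected model is imprecise.** A typical practice has 4.43/2 = 2.22 patients per arm. With residual SD 3.3 × √0.95 = 3.22, the standard error of one practice's own treatment difference is 3.22 × √(2/2.22) = 3.1 points, more than twice the MCID.

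**The case against.** The strongest defence is that the protocol uses shorthand. It does not say that the practice effect is an intercept only, the stated purpose points towards a random slope, and 11.4 leaves the detailed description of analyses to an SAP that is not shown. That SAP may well contain the right model. This softens the point but does not remove it. The protocol has gone beyond leaving the model open: it names one and says what it is for. An SAP that follows the text inherits the mismatch, and one that corrects it departs from the text.

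A second objection is that the corrected analysis would yield little. This stands in large part: the simulation detected a between-practice SD equal to the MCID in about one trial in six, and gave a median estimate of 1.2 when the truth was zero. It is a good argument for the alternative fix of restating the aim.

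A reader might also infer three stronger points that the protocol does not support:

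- *That the model drops the primary covariates.* The sentence names no fixed effect other than treatment, but nothing says that the covariates are removed, and the complete-case and per-protocol items do not restate them either. Nor would it follow that any difference from the primary result comes only from lost adjustment, because a practice intercept also changes the weighting of patients.
- *That standard errors in the primary ANCOVA are too wide because it ignores practice.* This needs balanced packs. The protocol says "All participating GPs will receive a package with the required and pre-randomized medication necessary to recruit up to 10 participants", but neither 8.8 nor 6.2.1, 7.3 or 8.1.3 says that a pack is balanced or blocked. At assumed ICCs of 0.02, 0.05 and 0.10, packs of five and five would give a standard error with a practice intercept of 0.995, 0.985 and 0.967 times that without. Under a simple 1:1 list the ratios are about 0.999, 0.995 and 0.98, and the true standard error without the intercept is 0.9998, 0.9995 and 0.9987 times its model-based value, so the ANCOVA standard error is essentially correct. Adding practice to the primary model is a preference, not a correction.
- *That 11.2 is in error for counting ICC as a loss of power.* Changing that wording would alter no figure.

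**Conclusion.** Wrong as written, in an exploratory sensitivity analysis. The named model sets the between-practice variance of the treatment effect to zero, so it cannot address the aim given in the same list item. This follows from the algebra on the plain reading of practice as a random intercept and needs no assumption about the data. The simulated detection rates are less firm: they rest on the assumed ICC of 0.05, an even spread of patients over practices and only 60 trials per scenario, and serve only to show that large heterogeneity alone would be detectable.

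The consequence is limited to what the report could claim about consistency across practices. The primary ANCOVA, its test and N=204 are untouched.

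**What to change.** Choose one of two changes in 11.4.2, and carry it into the SAP before unblinding.

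1. **Keep the aim and change the model.** Specify a linear mixed model with treatment and the primary ANCOVA covariates as fixed effects, a random intercept for practice and a random treatment slope by practice. Report the SD of the slope with its confidence interval. Naming the covariates makes the model comparable with the primary analysis. The interval matters more than the point estimate, given the median of 1.2 seen when the true SD was zero.
2. **Keep the model and change the aim.** State that the analysis accounts for clustering of outcomes by practice, and make no claim about variation in the effect. The covariates should be named here too.

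Either change costs about one sentence and needs no further data or patients. The drawback of the first is that, at about 4.4 patients per practice, the slope SD will be imprecise and may be estimated at zero. The text should say that a zero or non-significant estimate is not evidence of a uniform effect.

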#### 11.4.3 Secondary Analyses

The analysis of secondary outcomes will be of exploratory nature and results will be interpreted only for hypothesis generation. Summary statistics of cough-related QoL assessed by the LCQ score 7, 28 days, and 3 months after randomization, cough-related QoL sub-domains physical and psychological, and social 7, 14, 28 days, and 3 months after randomization will be presented in tables and figures. Total number and percentages will be calculated for overall cessation of cough 7, 14, 28 days, and 3 months after randomization, incidence rate of re-consultations at GP and/or hospitalizations within 3 months following randomization.

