### **4.3 Secondary Objectives**

To evaluate the impact of oral prednisone on:

- Cough-related QoL at other time-points (7, 28 days and 3 months after randomization)
- Three cough-related QoL (LCQ) sub-domains, i.e. physical, psychological, and social
- Overall cessation of cough, i.e. proportion of patients without cough symptoms 7, 14, and 28 days after randomization

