### **9.2.1 Assessment of primary outcome**

At baseline GPs will hand participants the LCQ and will be available to answer question. Participants will complete the LCQ on paper. For the follow-up the LCQ will be administered by trained research staff and recorded electronically.

The LCQ total score (addition of domain scores) ranges from 3-21; a higher score corresponds to a better health status (30). Total and individual domain LCQ scores will be calculated. Please also see section 5.1.

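### Section 11.4.3 assigns the secondary LCQ outcomes summary statistics and names no adjusted between-group estimate or confidence interval, although Section 4.3 asks for the impact of prednisone and baseline LCQ is collected

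*Protocol*

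**What the plan says.** Section 4.3 introduces the secondary objectives with "To evaluate the impact of oral prednisone on" and lists LCQ at days 7 and 28 and at 3 months, together with the physical, psychological and social domains. The study schedule has the LCQ completed at day 0 and at every follow-up call. Section 9.2.1 adds "Total and individual domain LCQ scores will be calculated".

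For the day-14 total score, Section 11.4.2 specifies an ANCOVA and a treatment effect with 95% CI: "Covariates of the ANCOVA model will be baseline LCQ scores, duration of cough, age, sex, and smoking status".

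For the other LCQ outcomes, Section 11.4.3 says that the secondary analyses are exploratory and serve hypothesis generation. It then gives the method: "Summary statistics of cough-related QoL assessed by the LCQ score 7, 28 days, and 3 months after randomization", and the same for the three domains at days 7, 14 and 28 and month 3, in tables and figures. No model, group difference, interval or covariate is named. Section 11.4 leaves the detailed description of analyses to a SAP, which is not at hand.

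**The concern.** Impact is a between-group quantity. Means and SDs by arm describe each group, but they do not state the difference or its uncertainty. A reader who wants to know whether there is an effect at day 7, at month 3 or in one domain would have to construct the comparison.

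Any comparison built from arm summaries alone would be unadjusted. It would carry a chance baseline difference in LCQ or cough duration into the result and would be less precise than the adjusted day-14 estimate. Section 6.2.1 describes a 1:1 list and mentions no stratification, so nothing in the stated design balances baseline LCQ. The same instrument would be analysed one way at day 14 and a weaker way everywhere else, although the data needed for adjustment are already collected.

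**Working it through.** **1. Outcomes affected.** Total score at 3 times plus 3 domains at 4 times: 3 + 3 × 4 = 15.

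**2. Inputs (Section 11.2).** Difference 1.3 points; SD 3.3 ("We decided to use the more conservative assumption of 3.3 points"); two-sided alpha 5%; power 80%; 102 per arm; drop-out 10%. The only baseline to follow-up correlation given is rho = 0.4. It belongs to an alternative scenario with SD 2.9 and is not tied to a time point.

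**3. The plan's own figure.** The protocol states: "To be able to detect an MCID of 1.3 points with a power of 80%, a total of N=204 patients need to be recruited". Normal approximation: n per arm = 2 × (1.96 + 0.842)² × 3.3² / 1.3² = 101.2, rounded up to 102, so 204 in total. The exact t calculation gives 103 per arm, with power 80.0% at 102. The figure reproduces.

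**4. Effect of baseline adjustment on precision.** Residual variance = SD² × (1 − rho²); the interval width scales with √(1 − rho²).
- rho 0.4: 1 − 0.16 = 0.84, so variance falls 16%; √0.84 = 0.917, so the interval is about 8% narrower.
- Total score, SD 3.3, 102 per arm: unadjusted half-width 1.96 × 3.3 × √(2/102) = 0.91; adjusted 0.91 × 0.917 = 0.83.
- After 10% drop-out (91.8 per arm): 0.95 unadjusted, 0.87 adjusted.

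**5. Range over rho (assumed, because the protocol gives no value by time point).**

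| rho | √(1 − rho²) | Interval narrower by |
|---|---|---|
| 0.2 | 0.980 | 2% |
| 0.3 | 0.954 | 5% |
| 0.4 | 0.917 | 8% |
| 0.5 | 0.866 | 13% |
| 0.6 | 0.800 | 20% |
| 0.7 | 0.714 | 29% |

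The value 0.4 is itself uncertain. With SD 2.9 and rho 0.4 the protocol states N = 120, but the factor 1 − rho² gives 132 (normal) or 134 (t). N = 120 corresponds to rho = 0.5 in the t calculation.

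**6. Chance imbalance.** Assume that baseline SD is also 3.3. The SE of the baseline difference is 3.3 × √(2/102) = 0.46, so an imbalance of 1.96 × 0.46 = 0.91 points lies at the 95% bound. With equal SDs the regression slope equals rho, so an unadjusted comparison would shift by 0.4 × 0.91 = 0.36 points. That is 28% of the 1.3-point MCID.

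**7. Limit for the domains.** Section 9.2.1 gives the total as the sum of three domains with range 3 to 21, which implies about 1 to 7 per domain. The largest possible SD on such a scale is about (7 − 1)/2 = 3.0. Neither SD 3.3 nor the 1.3-point difference can therefore be carried to the 12 domain outcomes. Only the relative narrowing in step 5 can, and only if the assumed rho applies.

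**The case against.** The best defence is that these outcomes are explicitly exploratory, that Section 11.4 leaves detail to the SAP, and that models for such outcomes are commonly written there. Section 11.4.3 does not say that summaries are all that will be given, nor that they will be unadjusted.

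Part of this stands. A reader might infer that the protocol rules out baseline adjustment or any effect estimate. It does not: it leaves them unnamed. A reader might also infer a loss of 6 to 7 percentage points of power. The arithmetic exists: with SD 3.3 and rho 0.4, power for 1.3 points goes from 80.0% to 86.3% at 102 per arm (+6.4), and the gain is 6.9 points after 10% drop-out. But no secondary test or power is planned, so there is no power to lose. The protocol pairs rho 0.4 with SD 2.9, which gives 4.5 to 5.4 points. Over rho 0.2 to 0.7 at SD 3.3 and 102 per arm, the gain runs from about 2 to 18 points. The effect and SD are those of the day-14 total score. Nor are raw and adjusted results on different scales: both are in LCQ points and, under randomisation with a linear model, estimate the same mean difference. Arm means, SDs and counts would also let a reader derive an unadjusted difference and interval.

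Two things do not stand. Deferral to the SAP does not cure a method that the protocol itself states. Section 11.5 says expressly that the imputation procedure will be defined in the SAP, whereas Section 11.4.3 names its method and has no such pointer. Exploratory status does not explain the gap either: Section 11.4.2 calls its smoking subgroup analysis fully exploratory and still uses an interaction test.

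**Conclusion.** The point holds as a mismatch between objective and stated method. Section 11.4.3 assigns 15 LCQ outcomes summary statistics and names no between-group estimate, interval or baseline adjustment, while Section 4.3 asks for impact and the baseline scores are in hand.

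The gain from correcting it is precision and protection against chance baseline imbalance. At rho 0.4 the interval is about 8% narrower (0.91 to 0.83 points for the total score at SD 3.3 and 102 per arm); over an assumed rho of 0.2 to 0.7, about 2% to 29%. These figures consider baseline LCQ alone. The absolute figures apply the day-14 planning SD to the total score at other times. The protocol gives no SD, MCID or correlation for the domains or for days 7 and 28 and month 3. The correlation may well be lower at 3 months, where the gain would be smaller. The primary analysis is unaffected.

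**What to change.** In Section 11.4.3, add that each secondary LCQ outcome will be analysed with the Section 11.4.2 ANCOVA. Use the matching baseline score (total for total, domain for domain) and the same other covariates: duration of cough, age, sex and smoking status. Report the adjusted mean difference with 95% CI, labelled exploratory and not multiplicity-controlled. Keep the raw summaries by arm as the descriptive table. If the SAP already contains such a model, align Section 11.4.3 with it before unblinding.

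The cost is a sentence or two and re-use of the primary-analysis code. No new data are needed, and the primary error rate is unchanged. The downside is 15 further intervals: if there were no effect anywhere, 15 × 0.05 = 0.75 of them would be expected to exclude zero by chance, which is why the label matters.

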#### 11.4.4 Interim analyses

No interim analysis will be performed.

#### 11.4.5 Safety analysis

Total number and percentages will be calculated for incidence rate of re-consultations at GP and/or hospitalizations within 3 months following randomization, and total AE and SAE stratified by WHO-UMC causality categories (16) within 3 months after randomization.

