allergic reactions to the study drug, psychotic, or pre-psychotic episode, or Serious Adverse Events (SAE), sepsis, venous thromboembolism, fracture, can occur (27). In terms of side effects, a recently published retrospective cohort showed even a short time use of corticosteroids increases the incidence of severe adverse events such as sepsis or venous thromboembolism (28). Therefore, safety issues even with short time corticosteroids regimens are crucial. We feel that using the follow-up proposed for our trial will mitigate these concerns. A certain reassurance in terms of safety comes from the randomized-controlled trial conducted by Hay (17). In this study, assessing the effects of oral corticosteroids for acute lower respiratory tract infection in adults without asthma (prednisone 40mg once daily for 5 days, i.e. same dose as in our trial), no serious adverse events were observed (17). In any of the cases of adverse events occurring, as well as when other urgent reasons arise (pregnancy, new cancer diagnosis, infection other than URTI) (27), prednisone treatment will be stopped immediately. Other side-effects have been documented during short-term prednisone treatment: increase of appetite and activity, increased risk of infection, headache, glucose metabolism disorder (28). Study participants will be followed-up at several time points from enrolment in the study and experienced and trained study staff will call patients on day 7, 14, 28 and at 3 months and will ask participants to answer questions about outcomes and also the occurrence of AE or SAE. At the time of enrolment, participants will also be advised by their GP to contact the family practice or the study team in the event of any side-effects. We think that using the follow-up proposed for this study will mitigate the safety issues potentially posed even with short time corticosteroids.

Patients will not receive any financial compensation for study participation as the burden for them is minimal and they do not have any additional expenses for travelling, medical devices or other items.

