## **4. STUDY OBJECTIVES**

### **4.1 Overall Objective**

The purpose of this study is to assess whether a 5-day treatment with orally administered prednisone provides patient-relevant benefits by improving the cough-related QoL of patients with post-infectious cough triggered by an URTI and seeking care in adult primary care practices. The study aims to describe an efficacy and safety profile for a 5-day prednisone treatment compared to a 5-day course of placebo.

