### 5.4 Safety Outcomes

- Incidence rate of re-consultations at GP and/or hospitalisations within 3 months following randomisation
- Total AE within 3 months after randomization
- SAE within 3 months after randomization
- Changes in glucose levels for patients with pre-study controlled diabetes that are deemed by GP to exceed the hypothesized benefit on cough.

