## 8.2 Administration of experimental and control interventions

### 8.2.1 Experimental Intervention

Two tablets of PREDNISON Galepharm Tabl. 20 mg will be taken orally by the patient once daily during breakfast. The intervention group will receive prednisone for five days. Follow-up time will be 3 months from the start of treatment. In the event of a missed dose, patients are instructed to continue medication intake on the next day. Please see Appendix OSPIC Medication Guide\_V1.0.

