## 9.2 Assessments of outcomes

On days 7, 14, and 28 and at 3 months patients will be called by a trained and experienced research staff/study nurse, and asked to complete the LCQ on the phone. Appointments for the next phone calls will be set during the previous phone call. At the follow-up phone calls the research staff/ study nurses will also inquire about the presence of cough (binary variable yes/no), adherence (day 7), number of re-consultations with the GP, hospitalisations for potential illness deterioration and the occurrence of AE and SAE events. Incidence rates of AE and SAE will be assessed in WHO-UMC (16) causality categories “certain”, “probable”, “possible”, and “unlikely” during 3 months following randomisation.

In case the phone is not answered, follow-up phone calls will be performed several times over the next days: at day 7 (+ 2 days), at day 14 (+2 days), and 28 (+2 days) and at 3 months (+7 days). Participants will also be sent reminder email provided the email was given by the participant. Data at follow-up will be recorded with eCRF. For each enrolled study participant, an eCRF is maintained. eCRFs must be kept current to reflect subject status at each phase during the course of study. Participants must not be identified in the eCRF by name or initials and birth date. Appropriate coded identification (patient ID) is used. GPs and the research staff/study nurses will be authorized to do paper and eCRF entries. Source data will be available at all GPs to document the existence of the patients. To ensure uniform questioning during the trial (LCQ) and to minimize differences GPs and research staff/study nurses will receive a trial specific training and standard operating procedure leaflet prior to study start.

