### **9.2.4 Assessment of safety outcomes**

#### **9.2.4.1 Adverse events**

Corticosteroid potential side effects and complications are systematically recorded from the time of randomization (inform consent obtained at baseline) until the last follow-up calls at 3 months from randomization. Participants are informed and asked to immediately contact the GP or the study team in case of any possible side-effects. In case participants cannot reach the GP, they should visit the nearest hospital. This information is provided verbally and in writing to patients (Appendices Studieninformation\_OSPIC\_V1.0 and OSPIC Medication Guide\_V1.0). For safety reasons, the study team will also contact the corresponding GP to ensure patient follow-up is arranged as soon as possible. In case of persistent coughing at 3 months from randomization, the patient will be advised to visit the GP again for new assessment and necessary further investigations.

GPs and research staff/study nurses are instructed to document time of onset, duration, resolution, actions to be taken, assessment of intensity and relationship with study treatment. See section 10 (Safety) for AE definition and procedures.

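### AEs and SAEs are summarised only over one 3-month window after a 5-day course; counts by recorded onset should be added beside the 3-month totals

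*Protocol*

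**What the plan says.** - **Exposure and follow-up.** Section 8.2.1: "The intervention group will receive prednisone for five days. Follow-up time will be 3 months from the start of treatment". Section 8.2.2 says the same for placebo.
- **Outcome.** Section 5.4 lists "Total AE within 3 months after randomization", with SAEs over the same period. The synopsis and sections 4.4 and 9.2.2 use this window too.
- **Analysis.** Section 11.4.5 plans totals and percentages for "total AE and SAE stratified by WHO-UMC causality categories (16) within 3 months after randomization". It names no shorter window.
- **Scope.** Section 10.1 limits collection to AEs of special interest listed on the follow-up form, plus all SAEs. It expects low incidence and gives no rate.
- **Timing data.** Under section 9.2.4.1, GPs and study staff are "instructed to document time of onset, duration, resolution, actions to be taken, assessment of intensity and relationship with study treatment". Section 3.7 says staff "will call patients on day 7, 14, 28 and at 3 months and will ask participants to answer questions about outcomes", and AEs and SAEs are among the topics asked about. The schedule in section 9.1 confirms this for all four calls.
- **Aim.** Section 4.1: "The study aims to describe an efficacy and safety profile for a 5-day prednisone treatment".

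**The concern.** Section 3.7 describes appetite and activity changes, headache, infection risk and glucose disturbance as effects documented during short-term prednisone treatment. If such effects appear, many would be expected during or soon after dosing. The planned summary adds those days to about 12 further weeks in which neither arm takes study drug. Events unrelated to the drug accumulate at a similar rate in both arms over that time, and this pulls the ratio of the two risks toward 1.

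Readers will look to the 3-month percentages for the safety profile of the course. A true early excess would look smaller there than in the period when it arose. The data to show it are collected, but the stated outcomes and analysis do not use the timing. By contrast, section 11.4.3 tabulates cough cessation, asked about in the same calls, at all four times.

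**Working it through.** The protocol states no rate, power or precision for the safety analysis, so there is no figure of its own to reproduce. The check has two parts.

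**1. Share of the window off drug.** Inputs: 5 treatment days (section 8.2.1) and 3 months taken as 91 days.

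91 − 5 = 86 days; 86 / 7 = 12.3 weeks; 86 / 91 = 94.5%.

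**2. Dilution of the risk ratio.** These inputs are assumptions, because the protocol gives none:
- B is the proportion of control patients with at least one counted event over 91 days, arising at a constant hazard. Values tried: 5%, 10%, 30%, 50%.
- q is the extra risk from the drug, all of it arising early. The main value is 10%; 5% and 15% are also tried.

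Formulas:
- hazard h = −ln(1 − B) / 91
- control risk to day t: c(t) = 1 − exp(−h·t)
- active risk: a(t) = 1 − (1 − c(t))(1 − q)
- risk ratio: a(t) / c(t) = 1 + q(1 − c(t)) / c(t), which falls as c(t) grows

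Worked example for B = 10%, q = 10%:
- h = 0.10536 / 91 = 0.001158.
- Day 14: c = 1 − exp(−0.01621) = 0.0161; a = 1 − 0.9839 × 0.90 = 0.1145; ratio 7.1.
- 3 months: c = 0.100; a = 1 − 0.90 × 0.90 = 0.190; ratio 1.9.

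Results for q = 10% (active v control, risk ratio):

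| B | To day 7 | To day 14 | 3 months |
|---|---|---|---|
| 5% | 10.4% v 0.4%, 26.3 | 10.7% v 0.8%, 13.6 | 14.5% v 5.0%, 2.9 |
| 10% | 10.7% v 0.8%, 13.3 | 11.4% v 1.6%, 7.1 | 19.0% v 10.0%, 1.9 |
| 30% | 12.4% v 2.7%, 4.6 | 14.8% v 5.3%, 2.8 | 37.0% v 30.0%, 1.2 |
| 50% | 14.7% v 5.2%, 2.8 | 19.1% v 10.1%, 1.9 | 55.0% v 50.0%, 1.1 |

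Other values of q, 3 months against day 14:
- q = 5%: 1.45 against 4.1 at B = 10%; 1.05 against 1.4 at B = 50%.
- q = 15%: 2.35 against 10.2 at B = 10%; 1.15 against 2.3 at B = 50%.

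The risk difference, q(1 − c(t)), is diluted less. For q = 10% it goes from 9.8 points at day 14 to 9.0 at 3 months when B = 10%, and from 9.0 to 5.0 when B = 50%.

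In expected patients with 102 per arm (section 11.2), B = 10% gives about 11.7 v 1.6 to day 14 and 19.4 v 10.2 over 3 months. The early control cells are small.

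**The case against.** **Causality categories already separate drug events.** This is the strongest point. The sentence in section 11.4.5 stratifies by causality, so a reader who infers that harm is judged only on undifferentiated pooled events goes too far. Section 5.4 also lists re-consultations and/or hospitalisations, and glucose changes. But causality is assigned event by event, by staff who are blinded under section 6.2.2. A headache or an infection in a coughing patient can easily have another cause. Comparing randomised arms by onset needs no such judgement. The split mitigates the dilution without removing it.

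**Background may be low.** A reader might infer that every intercurrent illness is counted and that background events, especially in winter, swamp the drug's effect. The protocol does not support this. Collection is restricted to AEs of special interest and SAEs, incidence is expected to be low, and recruitment spans 18 months. At B = 10% and q = 15% a formal 3-month comparison (102 per arm, two-sided 5%) would still have about 74% power. Dilution keeps its direction at low background but may be modest.

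**The model puts the drug effect early, and no test is planned.** Both are true. The figures show what happens if harm is early; they do not show that it is. Section 11.4.5 is descriptive, so power is not the measure of the problem.

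**Late events matter.** This stands. Section 3.7 names sepsis, venous thromboembolism and fracture and relies on the whole follow-up. It rules out making an early window the main comparison.

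**Windowed tables are SAP content.** Section 11.4 leaves detail to an SAP that is not shown and may add them. The 3-month window, however, is fixed in the outcome definition and not left open.

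**Conclusion.** The point holds as an improvement to the planned presentation. The 3-month totals are a legitimate safety outcome; what is missing beside them is a comparison of the arms by time of onset. With 10% added early risk, the 3-month risk ratio would be 1.9 where the day-14 ratio is 7.1 (10% background), or 1.1 where it is 1.9 (50% background). These figures assume a constant background hazard, a wholly early drug effect and rates that the protocol does not supply. The direction is the same at every value tried, but the size in this trial is unknown.

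It does not follow that the safety analysis is invalid, that a harm would be hidden, or that the 3-month total should become secondary.

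**What to change.** Leave the 3-month AE and SAE outcomes in section 5.4 as defined, with their present standing. Add to sections 5.4 and 11.4.5 the number and percentage of patients per arm with AEs, and separately SAEs, by recorded onset: to day 7, days 8–14, days 15–28, and day 29 to month 3. Assign events by onset date rather than by the call at which they were reported, since calls may run late. State that a patient with events in several intervals counts once in each, so the columns need not sum to the 3-month total. Keep the causality split.

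The cost is a few extra table columns, some with small counts that should be read descriptively. No new data, calls or patients are needed. Label: cheap improvement.
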